### 2.2 Intervention and technological devices description

All patients will receive conventional treatment consisting of two daily one-hour sessions over 4 weeks, including traditional rehabilitation activities like range of motion exercises (passive, active assisted and active), progressive resistive exercises, balance and strength training, and aerobic conditioning. For the patients additionally participating in the RAT or VR-based rehabilitation, part of the duration of the whole treatment will be dedicated to the use of the devices, resulting in the same amount of rehabilitation for all participants. According to the technological device implemented (i.e., RAT or VR-based treatment), the intervention procedures and the related eligibility to participate will be checked according to the technology-specific guidelines and recommendations as appropriate [41–43]. The intervention will be delivered following the routine multidisciplinary clinical practice of the Institution where the study will be conducted [44]. Specifically, for each patient, the clinical care pathway will be based on the integration of the International Classification of Diseases (ICD) and the International Classification of Functioning Disability and Health (ICF) models as recommended by the WHO framework [45]. Therefore, adopting a biopsychosocial approach, the rehabilitation procedures will be adapted according to the patient’s medical diagnosis, disability severity, and rehabilitation objectives in favor of an individualized rehabilitation project and program. Therefore, if necessary, patients may undergo parallel rehabilitation activities that will involve different healthcare professionals (i.e., occupational therapists, speech therapists, psychologists).

Technology-based rehabilitation will be delivered through the following exoskeleton or non-immersive VR devices.

#### Lokomat®

The Lokomat (Hocoma AG, Switzerland) is a commercially available device consisting of a motorized exoskeleton facilitating symmetric gait patterns by the integration of computer-controlled linear actuators on patients’ hip and knee joints and a body-weight support treadmill system (BWTS). The device also provides pace and driving force adjustment according to each patient’s individual needs, as well as hip and knee stiffness and isometric strength monitoring. Increased feedback through a screen displaying non-immersive VR is supplied.

#### Armeo-Spring®

The Armeo-Spring (Hocoma AG, Switzerland) is a commercially available exoskeleton device for integrated arm and hand therapy. It is a three-dimensional, passive, exoskeleton robot that provides gravity compensation, offsetting the device and the patient’s upper limb with the help of a spring in place of robotic actuators. A screen displaying game-based VR environments to interact with during the therapy session is also integrated.

#### ProKin 252

The ProKin (TecnoBody SRL, Italy) is a proprioceptive-stabilometric assessment and training machine. It consists of a mobile platform including an electro-pneumatic system that employs an electronic pressure regulator to allow for independent stability control on the two axes of antero-posterior and lateral movements. The joint motion data, collected in the kinesthetic trace, is displayed on an integrated monitor that simultaneously provides game-based non-immersive VR exercises. The system can therefore provide sensory-motor monitoring along with both static and dynamic (monopodalic or bipodalic) balance training with real-time biofeedback.

#### D-Wall

The D-Wall (TecnoBody SRL, Italy) is a digital mirror device consisting of a strength platform paired to a control PC and a high-resolution 3D Kinect camera equipped with infrared rays that allows for motion-capture. The system provides immediate feedback of a patient’s movements on a large LCD monitor delivering VR-based mirror therapy and game-based exercises. The software includes different programs with different difficulties that can provide specific non-immersive VR-based recovery programs for ankle, lower limbs, trunk, shoulder, and upper limb rehabilitation.

#### Walker View

The Walker View (TecnoBody SRL, Italy) consists of a treadmill equipped with a control PC, a large LCD monitor, and an integrated 3D Kinect camera for motion capture. The detection load surface system of the treadmill, together with the motion-capture device, makes it possible to collect data on a patient’s balance and motion. Through the monitor, the patient is provided with biofeedback on gait analysis and non-immersive VEs to interact with during the training. Moreover, the device includes a body-weight support system ensuring locomotion therapy for patients at high risk of falls.

#### Riablo^TM^

The Riablo (CoRehab, Italy) is a medical device consisting of wearable sensors to don on patients’ limbs, and a stabilometric platform that transmits motion data to a software that provides biofeedback and displays non-immersive VR games through a screen. The system makes it possible to monitor and train a patient’s limb range of motion, balance, and anterior-posterior and lateral flexion and extension of the spine with the sensor placeable in the lumbar area. The device was designed to address orthopedic and neuromotor conditions to facilitate passive and active mobility and proprioceptive capacity recovery.

### 2.3 Data collection

Following preliminary collection of the socio-demographic (i.e., age, gender, living conditions, marital status, occupation, caregiver identification, and education) and clinical (i.e., BMI, primary diagnosis, comorbidities, health-related risk factors, and COVID-19-related anamnesis) characteristics, patients will undergo a multidimensional evaluation. This will include the functional status, cognitive functioning, perceived HRQoL and psychological aspects. All patients will be also asked to report any prior experience in using technological devices during rehabilitation. Moreover, the same information will be collected from the therapists involved, along with their individual socio-demographic and occupation-related data (i.e., age, gender, occupation, and overall seniority).

#### 2.3.1 Functional status

*Modified Barthel Index (MBI)*. The MBI is a 100-point rating scale measuring a patient’s ability to perform 10 different types of ADLs (i.e., chair/bed transfer, ambulation, stair climbing, toilet transfer, bowel control, bladder control, bathing, dressing, personal hygiene, feeding). Each activity is assigned a numeric value in accordance with the patient’s assistance needs. Lower scores indicate less independence, whereas higher scores reflect greater independence [46]. This scale has been widely used in the hospital setting and, compared to the original version (the Barthel Index scale–BI), it has been shown to be test-retest reliable in the rehabilitation context [47].

*Morse Fall Scale (MFS)*. The MFS is a reliable and validated tool to measure patient’s risk of falls. It consists of six items exploring: the patient’s history of falls (immediate or within 3 months), any secondary diagnosis, any need for ambulatory assistance, if the patient receives intravenous therapy, the patient’s gait and ability to transfer, and the mental status (orientation). The total score ranges from 0 to 125 with higher scores reflecting a greater risk of falling (0–24: no risk; 25–44: low risk; ≥45: high risk) [48].

*Stratify Scale*. The stratify Scale is a validated 5-point tool measuring patient’s risk of falls. For the current study, this instrument will be administered to those patients with a higher risk of falling (MFS ≥ 45). It comprises five items providing further insight on the following risk factors: past history of falling, patient agitation, visual impairment, incontinence, transfer and mobility. From the original validation, a predictive cut-off score of risk of falling was fixed at ≥ 2 points [49].

*Functional Independence Measure (FIM)*. The FIM is a widely used and reliable functional assessment tool generally adopted in rehabilitation as a functional outcome indicator. It evaluates a patient’s disability level indicating the degree of assistance required in the ADLs. It comprises 18 items. Of these, 13 consider motor and 5 cognitive domains. All items are measured on a 7-point Likert scale with a total score ranging from 18 (complete dependence) to 126 (complete independence). Two sub-scores can be calculated: FIM motor (range: 13–91) and FIM cognitive (range: 5–35) [50, 51].

*Timed Up & Go Test (TUG)*. The TUG is a functional test measuring a patient’s risk of falling, as well as static and dynamic balance. Specifically, it measures the time a patient takes to stand up from an armchair, walk forward 3 m, turn, walk back to the chair, and sit down. The longer the time this takes, the higher the risk of falling, evaluated with a cut-off score that varies according to the clinical population [52].

*Basic Activities of Daily Living (BADL)*. The BADL is a rating scale assessing a patient’s level of independence in the basic activities in relation to the daily environment (i.e., bathing, dressing, toilet, continence, transferring, feeding). It comprises a total of six items scored on a 3-point scale. Higher scores indicate stronger independence in basic ADLs [53].

*Instrumental Activities of Daily Living (IADL)*. The IADL provides an assessment of a person’s level of independence in performing more complex and instrumental activities (i.e., using the telephone, making purchases, cooking, housekeeping, doing laundry, handling money, using means of transport, responsibility for his/her own medications). Higher scores reflect stronger autonomy in more complex ADLs [54].

*Global Perceived Effect (GPE)*. A single item evaluating the perceived efficacy of the treatment will be administered at the end of the intervention. Patients will be asked to rate, on a scale ranging from 1 to 7, how much their condition has improved or deteriorated following the treatment they received. To check item responsiveness, the same numerical scale will also be administered to the therapists involved to evaluate how much patients’ conditions have changed following the intervention provided [55].

#### 2.3.2 Cognitive functioning

Montreal Cognitive Assessment (MoCA)

The MoCA is a widely used screening test covering eight cognitive domains: visuospatial abilities, executive functions, attention, concentration, short-term and delayed verbal memory, working memory, language, and orientation to time and space. This test has shown satisfactory psychometric properties including high sensitivity and specificity to identify cognitive impairment in a wide array of diseases [40]. The pre- post-intervention change will be estimated by administering the alternate validated form of the test [56]. Moreover, the telephone-based version of the MoCA (T-MoCA) will be administered at the 6-month follow-up [57].

*Symbol Digit Modalities Test (SDMT)*, *Oral version*. The SDMT measures speeded information processing by evaluating a patient’s attention, perceptual and motor speed, and visual scanning. The patient is given a sheet with nine symbols, each paired with a number on top of the page. A randomized and sequential assortment of these symbols are presented on the remainder of the page. Within 90 seconds, the patient is asked to scan each symbol and verbally respond with the corresponding number [58].

Trail Making Test (TMT)

The TMT comprises two parts (TMT-A and TMT-B). The TMT-A consists of a standardized page with scattered numbers (from 1 to 25) within circles. The patient is asked to connect the numbers in ascending order as quickly as possible. Similarly, the TMT-B presents a standardized page including numbers (from 1 to 13) and letters (from A to N). The patient is instructed to connect the numbers and the letters in order and alternate them. While the TMT-A evaluates psychomotor speed and visual search attention skills (i.e., visual scanning, graphomotor speed, and visuomotor processing speed), the TMT-B measures executive function components (i.e., working memory, inhibition control, or set-switching abilities) [59].

*Stroop colour word test*. For the present study protocol, a shortened version of the Stroop test is used [60]. This tool consists of three parts measuring selective attention, cognitive flexibility and inhibition, and sensitivity to interference. In the first part, the patient is given a list of color words (i.e., red, blue, green) and is asked to read them as quickly as possible. In the second part, the same colors are presented as colored circles. Here, the patient is asked to name them. In the last part, a list of the same color words is presented printed in nonmatching colors. The patient is instructed to name the colors disregarding the verbal content of the words. The final score is obtained by computing the time interference effect (based execution time) and the error interference effect (based on number of errors).

Frontal Assessment Battery (FAB)

The FAB is a brief battery of six cognitive tasks to assess executive functions (i.e., conceptualization and abstract reasoning, lexical verbal fluency and mental flexibility, motor programming and executive control of action, self-regulation, resistance to interference, inhibitor control, and environmental autonomy). Each task is evaluated with a specific subtest. A total score of 18 points is obtainable, with higher scores indicating better performance [61].

Phonemic verbal fluency test

To evaluate phonemic fluency, a task-specific test belonging to a wider battery that measures cognitive deterioration will be implemented [62]. In this test, the patient is asked, in three different trials (each lasting 1 minute), to generate as many words as possible beginning with the letters “F”, “A”, and “S”. For each word generated, one point will be assigned. The higher the final score, the better the performance on the cognitive test.

#### 2.3.3 HRQoL and psychological status

EuroQoL-VAS (EQ-VAS)

The EQ-VAS is a widely used, reliable tool to quantitatively record a patient’s self-rated health. The patient is asked to respond on a vertical visual analogue scale (0 = the worst health you can imagine; 100 = the best health you can imagine) [63].

Short Form Health Survey-12 (SF-12)

The SF-12 evaluates functional health and well-being according to the patient’s perspective. It comprises 12 items measuring different health-related domains (i.e., physical functioning, general health, role physical, role emotional, vitality, bodily pain, social functioning, and mental health) generating two aggregate summary indexes: the physical component summary (PCS) score and the mental component summary (MCS) score, indicating physical health and mental health, respectively. Higher total scores indicate better health [64].

Generalized Anxiety Disorder-7 (GAD-7)

The GAD-7 is a validated questionnaire measuring the severity of anxiety symptoms in the previous two weeks. It is composed of 7 items scored on a 4-point Likert scale (0 = not at all; 3 = nearly every day). Higher scores indicate more severe anxiety symptomatology. Scores of 5, 10, and 15 represent the cut-offs for mild, moderate, and severe anxiety, respectively [65].

Patient Health Questionnaire-9 (PHQ-9)

The PHQ-9 is a validated questionnaire evaluating the severity of depression symptoms in the previous 2 weeks. It consists of 9 items scored on a 4-point Likert scale (0 = not at all; 3 = nearly every day). Higher scores indicate more severe depression symptomatology. Scores of 5, 10, 15, and 20 represent the cut-offs for mild, moderate, moderately severe, and severe depression, respectively [66]. A 4-item shortened version (PHQ-4) was developed, including two items of the GAD-7 and two of the PHQ-9, as a screening measure for both anxiety and depression symptomatology. This version will be implemented at the telephone-based 6-month follow-up [67].

*The Satisfaction-Profile (SAT-P)*. The SAT-P is a validated instrument to evaluate patient satisfaction in the last month with different domains associated with HRQoL. It is composed of 32 items evaluated on a 10-cm horizontal visual analogue scale ranging from “extremely dissatisfied” to “extremely satisfied”. For the present study protocol, three items will be included in the evaluation, specifically measuring personal satisfaction with mood, resistance to physical fatigue, and mental efficiency [68].

*Client-Centred Rehabilitation Questionnaire (CCRQ)*. The CCRQ is a validated questionnaire measuring a patient’s subjective experience of care in rehabilitation settings. It consists of 33 items scored on a 5-point Likert scale (1 = strongly agree; 5 = strongly disagree) and grouped into seven subscales (i.e., patient participation in decision making and goal setting, patient-centred education, evaluation of outcomes from the patient’s perspective, family involvement, emotional support, co-ordination/continuity, physical comfort). Reversed scoring is applied with higher scores reflecting a better rehabilitation experience [69].

#### 2.3.4 Technology evaluation

For the patients also participating in the technology-based rehabilitation program, the following additional questionnaires will be administered.

*Psychosocial Impact of Assistive Device Scale (PIADS)*. The PIADS is a checklist of 26 self-report items, presented as a list of common words or short sentences. It comprises three subscales (i.e., adaptability, competence, and self-esteem) evaluating the degree of acceptance related to the device as well as its impact on different domains of a patient’s subjectivity. Patients are asked to rate their degree of perceived satisfaction or improvement related to each item on a 7-point Likert scale. The score is meant to be either positive (+1, +2, +3 scores) or negative (-1, -2, -3 scores), with a central tendency marked as zero that indicates no perceived change after using the device. Higher scores reflect the technological device’s stronger psychosocial impact [70].

*System Usability Scale (SUS)*. The SUS is a widely used questionnaire to evaluate the perceived usability of systems and devices. It consists of 10 items measuring a device’s ease-of-use and learnability. For each item, the patient is asked to respond on a 5-point Likert scale (0 = strongly disagree; 4 = strongly agree). Total scores are converted into a percentile ranking (0–100) with higher scores indicating higher usability [71]. For the present study protocol, this tool will be administered to both patients and therapists. In addition, therapists will undergo a semi-structured interview aiming to collect qualitative data on the perceived usability of devices from a healthcare professional’s perspective. This data will be integrated to the scale.

*Experience in Technology-based Rehabilitation Schedule (ExTR)*. Based on a preliminary literature review [72], a schedule to evaluate patients’ experience of use of the devices in the rehabilitation program was developed. The ExTR aims to provide mixed-method information concerning different domains related to patient’s subjective experience of use (i.e., learnability, acceptability, usefulness, adaptability, adverse effects, engagement, enjoyment, safety, perceived effectiveness). The schedule includes 15 items scored on a scale ranging from 0 (not at all) to 4 (extremely). Higher scores indicate better experience of use. To provide further insight into the overall experience of use, an additional open-ended question was added at the end of the tool to elicit patients’ socio-cognitive and experiential factors related to the technology-based program (e.g., emotions, expectations, motivation, satisfaction).

### 2.4 Data management

Data collection is currently ongoing. The data collected throughout the study phases will be handled and stored in accordance with the General Data Protection Regulation (GDPR) 2018. The use of the study data will be controlled by the principal investigator. All data and documentations related to the study will be stored in accordance with applicable regulatory requirements and their access will be restricted to authorized personnel.

### 2.5 Ethics considerations

The current study protocol (PHTinRehab Study) was approved by the Ethics Committee of ICS Maugeri, Pavia Italy (February 2021, protocol n. 2517CE). All patients will be given the informed written consent to join the study, and asked to sign it. Their participation will be voluntary and will not affect the healthcare process. The entire study will be conducted in accordance with the Declaration of Helsinki and all relevant guidelines and regulations covering respect for the rights and dignity of participants.

### 2.6 Statistical analyses

Descriptive statistics will be conducted on participants’ socio-demographic and clinical characteristics, functional status, cognitive functioning, and HRQoL, and psychological status. Explorative analyses will be then conducted to estimate pre- post-treatment changes and long-term effects concerning the multidimensional evaluation performed. Particularly, these will be carried out by comparing patients who share the same medical disease and who experienced the use of the same technological device during rehabilitation. Within- and between-group pre- post-intervention differences will be tested with the paired-samples *t*-test and independent samples *t*-test, respectively. Additionally, a repeated-measures ANOVA test will be used to assess the longitudinal trajectories. Regarding technology evaluation, descriptive statistics will be conducted on devices usability, experience of use and psychosocial impact. Furthermore, post-hoc analyses will be performed to estimate the differences on technology evaluation in relation to the clinical condition and severity of participants. As for therapists’ devices experience of use, the semi-structured interviews will be analysed through inductive thematic analysis [73]. In conclusion, association analyses (e.g., correlations, regressions) will be carried out to explore the inter-relationships among all the variables measured. The Statistical Package for the Social Sciences (SPSS, version 28.0) will be implemented for data analyses. Sample size adequacy was estimated by resorting to power analysis [74], using G*Power Software Version 3.1.9.7 [75] on a repeated-measures ANOVA (within-between interaction) with three measurements, two groups, and a correlation among repeated measures of 0.5 (power: 0.80; α = 0.05). The required sample size to detect small-medium effect sizes (f = 0.20) was a minimum of 42 patients.

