### 2.1 Design, participants and procedures

The protocol has a prospective, two-arm, open-label, non-randomized study design (Fig 2). In a real-world clinical setting, patients will be consecutively enrolled according to the following eligibility criteria: 18 years of age or older; diagnosis of acquired brain injury (ABI; e.g., TBI, stroke), Parkinson’s Disease (PD) or orthopaedic disease (i.e., total hip/knee arthroplasty) requiring rehabilitation intervention; absence of a severe clinical condition (i.e., chronic heart failure at class IV according to the New York Heart Association classification—NYHA-IV, ischemic heart disease at class IV according to the Canadian Cardiovascular Society classification—CCS-IV, neoplastic diseases, acute respiratory diseases); no severe cognitive impairment (screened with the Montreal Cognitive Assessment–MoCA ≤ 15.5) [40]; no language disorders (e.g., aphasia); absence of severe mental health condition or psychiatric disorder (evaluated according to the Diagnostic and Statistical Manual of Mental Disorders—DSM-V) potentially compromising participation in the study; absence or withdrawal of the informed consent to participate.

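### The 80% power claimed for 42 patients belongs to one pooled two-group comparison, not to the same-disease, same-device comparisons that section 2.6 plans

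*Protocol article*

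**What the plan says.** All of this is in the protocol article.

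- **Sizing (2.6).** The power analysis is for a within-between interaction with "three measurements, two groups, and a correlation among repeated measures of 0.5" ("power: 0.80; α = 0.05"). The result is: "The required sample size to detect small-medium effect sizes (f = 0.20) was a minimum of 42 patients". Neither disease nor device enters the calculation.
- **Analysis (2.6).** The pre-post and long-term analyses, labelled explorative, are to be carried out by "comparing patients who share the same medical disease and who experienced the use of the same technological device during rehabilitation". Paired and independent-samples t-tests follow, then a repeated-measures ANOVA for trajectories.
- **Diseases (2.1).** Three groups are enrolled consecutively: acquired brain injury, Parkinson's disease, and hip or knee arthroplasty.
- **Devices (2.2).** "Technology-based rehabilitation will be delivered through the following exoskeleton or non-immersive VR devices": six are then described.
- **Arms (2.1).** One group has conventional treatment only; the other has conventional treatment plus robot-assisted or VR-based therapy. No allocation ratio is given.
- **Limitations (3.1).** The calculated sample is called limited and the evidence preliminary, in the context of generalizability.

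No quota, target or power is stated for any disease or any disease-device combination.

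**The concern.** The sizing and the analysis sentence describe different comparisons. The first treats the study as two groups; the second divides it by disease and by device. A power figure belongs to a particular test on a particular number of patients, so the 80% does not carry over to a comparison that uses only some of the 42.

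At stake is how the results can be read. If section 2.6 is followed as written, most change analyses will rest on far fewer than 42 patients, while the article presents the sample as adequate by power analysis. A non-significant result within one disease and one device would then say very little, and the text does not warn of that.

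The comparison sentence also has a drafting fault. Conventional-only patients used no device, so they cannot share one with anybody. Taken word for word, it does not describe the two-arm comparison for which the 42 was calculated.

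**Working it through.** **Inputs.** From section 2.6: f = 0.20, m = 3 measurements, k = 2 groups, correlation ρ = 0.5, α = 0.05, target power 0.80, stated N = 42. Assumed here: sphericity (ε = 1, which is needed to reproduce 42), 1:1 allocation as nearly as N allows, and the stratum sizes below, none of which the article gives.

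**Formula.** Noncentral F for the within-between interaction:

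- λ = f² × N × m / (1 − ρ) = 0.04 × N × 3 / 0.5 = 0.24 × N
- df1 = (k − 1)(m − 1) = 2
- df2 = (N − k)(m − 1) = 2(N − 2)

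**Step 1: the plan's own figure.** For N = 42, λ = 0.24 × 42 = 10.08 with df 2 and 80, and power is 0.803. For N = 41 it is 0.793 and for N = 40 it is 0.782. So 42 is correct for one interaction test that uses all 42 patients.

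**Step 2: the same test on part of the sample.** Only N changes.

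| Patients in the comparison | λ | df2 | Power at f = 0.20 |
|---|---|---|---|
| 42 (all) | 10.08 | 80 | 0.80 |
| 28 (two thirds of the sample) | 6.72 | 52 | 0.61 |
| 21 (half) | 5.04 | 38 | 0.47 |
| 14 (42/3, equal spread over diseases) | 3.36 | 24 | 0.32 |
| 8 (illustrative disease-device comparison) | 1.92 | 12 | 0.18 |

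**Step 3: the effect detectable with 80% power.** Solving the same formula for f gives 0.20 at N = 42, 0.36 at N = 14 and 0.51 at N = 8.

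**Step 4: what does not depend on the assumed sizes.** Power rises with N and first reaches 0.80 at N = 42. With a total of 42, a same-disease, same-device comparison keeps the stated power only if every patient falls into that single comparison. That does not fit consecutive enrolment of three diseases treated with six devices. Keeping 80% in just three such comparisons, one device per disease and each with its own controls, would take 3 × 42 = 126 patients.

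**The case against.** **The pooled test may still be planned.** A reader might infer that 42 is the sample for no planned test at all. The article does not support that. The abstract announces within-between interaction effects, section 2.1 defines two groups, and the ANOVA sentence in 2.6 does not repeat the disease and device restriction. A pooled two-group ANOVA is a fair reading. What stands is that the text leaves this open and attaches the restriction to the change analyses in general.

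**The comparator is not lost.** A reader might also infer that the restriction removes the control group. Section 2.1 names the conventional-only group, and 2.6 plans independent-samples t-tests between groups, so the intent is visible. This is a fault of wording.

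**The study is openly exploratory.** The analyses are called explorative, section 3.1 calls the evidence preliminary, and 42 is a minimum. This lowers the severity. It does not resolve the mismatch: 3.1 speaks of generalizability even once the required size is reached, which takes 42 to be adequate, and no larger target is given.

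**Stratum sizes are unknown.** This is correct. In particular, multiplying three diseases by six devices to get a per-cell count is not supported. Section 2.2 makes device use depend on technology-specific eligibility, Armeo-Spring trains the arm and hand while the orthopaedic group has hip or knee replacement, and the number of technology users is not stated. The conclusion in step 4 needs no such count.

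**Conclusion.** The concern holds as a mismatch between sample size and analysis. The sample size arithmetic is correct. The stated 80% power at f = 0.20 applies to one pooled two-group by three-time interaction on all 42 patients, and to no same-disease, same-device comparison with fewer than 42.

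The size of the shortfall depends on stratum sizes that the article does not give. With 14 patients split 1:1, power is about 32%, and 80% is reached only at f = 0.36. Even with 28 patients in one comparison it is 61%. These figures keep the article's f, ρ and α and assume sphericity. That the calculation is pooled is itself an inference, from the absence of any disease or device factor and from section 3.1 treating 42 as the size of the study.

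This should be fixed, but it does not undermine the design: the study is exploratory and non-randomized, and clearer text cures the problem.

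**What to change.** 1. In 2.6 and 3.1, state that the 80% power applies only to the pooled technology-versus-conventional interaction over three measurements. Name that contrast as the analysis the 42 patients support, with disease as a model term.
2. In the same places, state that same-disease, same-device comparisons are not powered (about 32% with 14 patients, given as an assumption) and will be reported as estimates with confidence intervals.
3. Reword the comparison sentence in 2.6 so that users of a given device are compared with conventional-only patients who have the same disease.

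The cost is a few sentences and a less favourable statement of power for the narrower comparisons. No extra patients are needed, and the disease- and device-specific descriptions that the article values are kept. Data collection is ongoing (section 2.4), so the change is best made before outcome data are examined.
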